#### Secondary outcomes analysis

Continuous secondary outcomes (e.g., headache intensity assessed by NRS, MMFIQ score, MSQ domains, HRV indices, acute medication use days) will be analyzed using the same MMRM analytical framework as the primary outcome measures and will be adjusted for baseline values. For outcome measures assessed at multiple time points, the same fixed-effects model structure (treatment group, time, and the interaction between treatment and time) will be used.

Given that this trial is a pilot study, all analyses are considered exploratory and are intended to generate hypotheses. Therefore, no correction for multiple comparisons will be performed for any secondary or exploratory outcome measures. All results will be reported with *p*-values, along with effect sizes and 95% confidence intervals. *P*-values will be reported descriptively to indicate the strength of the signal relative to sampling variability.

#### Exploratory and safety analyses

Exploratory Biomarkers/Imaging: Changes in serum biomarker levels (CGRP, estradiol, progesterone) and neuroimaging metrics will be analyzed using paired t-tests or Wilcoxon signed-rank tests within each group, and between-group comparisons will be made using ANCOVA. Correlation analyses (Pearson’s or Spearman’s) will explore relationships between clinical, autonomic, and biomarker/imaging changes. All exploratory findings will be reported with effect sizes and 95% CIs, and will be explicitly labeled as “exploratory, unadjusted for multiple comparisons, for hypothesis generation only” to prevent overinterpretation.

Safety Analyses: The incidence of adverse events (AEs) and serious adverse events (SAEs) will be summarized by treatment group, described by system organ class and preferred term. Differences in AE rates will be compared using Fisher’s exact test.

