## Objectives

The efficacy and safety of acupressure therapy for menstrual migraines have not yet been fully evaluated, and most existing acupuncture trials for MM have employed fixed protocols without phase-specific adjustments. Furthermore, no study has systematically integrated objective autonomic nervous system function, serum biomarkers, and neuroimaging findings to comprehensively assess the mechanisms underlying acupressure treatment for MM. To address these limitations, we designed this randomized exploratory trial to:(1) Evaluate the feasibility of a phase-specific sequential acupuncture protocol;(2) Assess the preliminary efficacy and variability of pressure-point acupuncture compared with the standard naproxen prophylaxis regimen, providing an effect size estimate for future sample size calculations;(3) Explore potential mechanisms of action through multidimensional autonomic, serological, and neuroimaging markers.

Importantly, this trial is an exploratory rather than a confirmatory study. The findings will inform the design of future large-scale, definitive randomized controlled trials. We hypothesize that, compared with naproxen, sequential pressure-needle therapy will show a clinically favorable trend and demonstrate good safety and tolerability, and that the observed changes in autonomic nervous system and biomarker results will provide mechanistic insights for subsequent studies.

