#### Comprehensive mechanism analysis

Correlation analysis using Pearson or Spearman will explore the relationships among the following items: changes in major clinical indicators, such as the number of days with moderate to severe headache; core autonomic nerve indicators, such as the LF/HF ratio; serum biomarker levels, such as calcitonin gene-related peptide, estradiol, P4; and indicators derived from neuroimaging, such as the functional connectivity strength in the target network.

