### Sample size

As this is a pilot feasibility study designed to estimate the effect size and variance of the primary outcome for a future definitive trial, no formal hypothesis-testing power calculation was performed. The sample size was determined with reference to previous multicenter randomized controlled trial of acupuncture for menstruation-related migraine (16, 17), which provided reference effect size estimates and variability data for this population. Based on the effect size reported in previous high-quality trials and clinical feasibility, we determined that 30 participants per group would provide a valid estimate of treatment response, variability, and retention (18). Assuming a 20% dropout rate during the trial, we planned to enroll 38 participants per group, with a total target sample size of 76. This sample size is sufficient to estimate key feasibility parameters and provides a preliminary basis for the design and sample size calculation of future confirmatory trials.

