#### Statistical methods

All analyses will be performed using both Intention-to-Treat (ITT) and Per-Protocol (PP) principles. A two-sided *p* < 0.05 will be considered statistically significant.

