Mechanistically, we anticipate that this stage-specific intervention will modulate pain-related brain networks and autonomic regulatory circuits. A growing body of neuroimaging evidence suggests that acupuncture can modulate functional connectivity in pain-processing regions, including the amygdala, insula, mesolimbic-parietal cortex, and temporal cortex (41), and can modulate the hypothalamic-limbic-brainstem circuit involved in autonomic control (23, 39, 42). Acupuncture has been shown to enhance connectivity between the amygdala/mediofrontal-parietal cortex and the middle temporal gyrus, as well as between the mediofrontal-parietal cortex and the superior temporal gyrus—regions that play a key role in multisensory pain modulation (41). Furthermore, a meta-analysis of resting-state fMRI studies further confirmed that acupuncture modulates the superior frontal gyrus, angular gyrus, and corpus callosum in migraine patients, and these changes are significantly associated with reduced pain intensity and headache frequency (43). Furthermore, the sustained preventive effects of acupuncture appear to involve influences on the default mode network, the anterior parietal network, the limbic system, and the descending pain modulation system (44). If these imaging changes are observed, they are expected to correlate with reduced headache frequency and improved autonomic balance, providing preliminary evidence for the central mechanisms of sequential pressure acupuncture therapy.

Compared to the control group receiving oral naproxen sodium, the sequential acupuncture therapy in the experimental group—as a non-pharmacological preventive measure—not only demonstrated better tolerability but also allowed for personalized, phased interventions tailored to the cyclical nature of menstrual migraines, aligning closely with the pathophysiological changes of the condition. This therapy avoids the gastrointestinal discomfort, neurological adverse reactions, and potential safety risks associated with long-term use of oral naproxen sodium (45). Unlike existing studies that focus solely on subjective clinical efficacy, this study innovatively integrates multidimensional assessments of objective autonomic nervous system function, serum biomarkers, and neuroimaging to systematically explore the core therapeutic mechanisms of sequential acupuncture therapy.

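### The mechanism reading rests on within-arm tests and change correlations that contain no treatment contrast, and is not tied to the between-arm analyses already planned

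*Protocol article*

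**What the plan says.** The third aim under Objectives is to explore how the therapy might work, and the hypothesis there is that "the observed changes in autonomic nervous system and biomarker results will provide mechanistic insights for subsequent studies".

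The Comprehensive mechanism analysis section consists of correlations only: "Correlation analysis using Pearson or Spearman will explore the relationships among the following items". The items are changes in clinical indicators, autonomic indices, serum markers and imaging measures. No arm term is stated.

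The Exploratory and safety analyses section names three tools for serum markers and imaging. Changes "will be analyzed using paired t-tests or Wilcoxon signed-rank tests within each group"; the arms are compared by ANCOVA; and "Correlation analyses (Pearson’s or Spearman’s) will explore relationships between clinical, autonomic, and biomarker/imaging changes". Each exploratory finding is to be labelled as unadjusted and meant only to generate hypotheses.

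Heart rate variability is a secondary outcome. Under Secondary outcomes analysis it has its own MMRM with treatment and treatment-by-time terms.

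The Discussion says of imaging changes, if seen, that "they are expected to correlate with reduced headache frequency and improved autonomic balance, providing preliminary evidence for the central mechanisms of sequential pressure acupuncture therapy". Its limitations paragraph states that there is no sham arm. Under Statistical methods, a threshold is set for all analyses: "A two-sided *p* < 0.05 will be considered statistically significant".

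**The concern.** The question is whether press-needle therapy acts on a marker. The only randomised evidence on that is the difference between the arms.

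- A within-arm paired test has the null of no change since baseline. It is false if the marker moves in both arms for any shared reason.
- A change-with-change correlation has the null that marker change and headache change are unrelated. It is false if the two move together for any reason, including the disease itself or the effect of naproxen.

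The protocol gives a reason to expect such a link. The Introduction attributes attacks mainly to falling estrogen and names CGRP release as part of that process, and estradiol and CGRP are both among the markers to be correlated.

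The Discussion sentence combines observed change with correlation and does not ask for a difference between the arms. A marker that behaves the same under press-needle and naproxen could then be reported as preliminary evidence of a press-needle mechanism, and carried into the confirmatory trial that this pilot is meant to inform.

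**Working it through.** **Inputs from the protocol.** Two-sided alpha is 0.05 (Statistical methods). Under Sample size, "30 participants per group would provide a valid estimate of treatment response, variability, and retention", and "Assuming a 20% dropout rate during the trial, we planned to enroll 38 participants per group, with a total target sample size of 76". Check: 30/(1 − 0.20) = 37.5, rounded up to 38 per arm, and 2 × 38 = 76, which reproduces the plan. No power or error rate is given for the mechanism analyses, so there is nothing further to reproduce.

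**Inputs assumed.** The protocol gives neither the common drift of a marker (d, in SDs of the change score) nor the correlation of marker change with headache change (rho). Both are varied from zero upwards. The joint simulation also assumes a marker test-retest correlation of 0.6. In every case the arm effect on the marker is set to zero.

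**Paired t-test in the press-needle arm, n = 30.** The rejection rate is P(|T| > t(0.975, 29)), where T is noncentral t with 29 df and noncentrality d√30. The critical value is 2.045.

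| d | noncentrality | rejection rate |
|---|---|---|
| 0 | 0 | 5% |
| 0.2 | 1.10 | 18.5% |
| 0.3 | 1.64 | 35.5% |
| 0.4 | 2.19 | 56% |
| 0.5 | 2.74 | 75% |

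**Pearson correlation of changes.** The test is t = r√((n − 2)/(1 − r²)) on n − 2 df, simulated 40,000 times per setting.

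| rho | pooled, n = 60 | one arm, n = 30 |
|---|---|---|
| 0 | 5% | 5% |
| 0.2 | 34% | 19% |
| 0.3 | 65% | 37% |
| 0.4 | 90% | 61% |

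Hand check at rho = 0.3, n = 60, by Fisher's z: atanh(0.3) × √57 = 0.3095 × 7.550 = 2.337, and Φ(2.337 − 1.96) = Φ(0.377) ≈ 0.65, which agrees.

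**All tests in the same simulated trials** (30 per arm, 5,000 runs per setting):

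| d | rho | paired | pooled correlation | ANCOVA arm term |
|---|---|---|---|---|
| 0 | 0 | 4.7% | 4.7% | 4.9% |
| 0.3 | 0.3 | 37% | 64% | 4.8% |
| 0.5 | 0.4 | 76% | 90% | 4.8% |

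Over all nine settings run, the ANCOVA arm term rejected in 4.8% to 5.5%. The Monte Carlo standard error at 5% is √(0.05 × 0.95/5000) = 0.3 percentage points, so this is consistent with the nominal level. With d = 0 and rho = 0, every test stayed near 5%, even when press-needle was given a 0.5 SD effect on headache days.

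**What cannot be computed.** Table 2 says that MRI is done in a subset but gives no size. The imaging rates would differ from those at n = 30 and n = 60.

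**The case against.** **The arms are already compared.** A reader might infer that mechanism evidence comes only from tests without a contrast. The documents do not support that: ANCOVA covers serum markers and imaging, and an MMRM covers heart rate variability. This objection stands. What remains is that the Comprehensive mechanism analysis section and the Discussion inference are not tied to those analyses.

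**The rejection rates are not error rates for the question asked.** A reader might take 65% or 90% against 5% as false positives. For the correlations that is wrong: if rho is truly 0.3, a significant result correctly detects an association. The problem arises only when the association is read as a press-needle mechanism.

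**The sizes are assumed.** They are, and at zero every test holds 5%. The biospecimen section also samples blood in the same two cycle phases before and after treatment, which limits cycle effects as a source of drift. Regression to the mean would reach these markers only indirectly, because women are selected on headache days. Large drift in blood markers should not be presumed.

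**Significance in one arm only.** A reader might infer that a result significant under press-needle but not under naproxen will be taken as a treatment effect. No section states such a rule, so no error rate is claimed for it.

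**Everything is labelled hypothesis-generating.** The label limits the harm and is meant to prevent overreading. It does not supply the missing contrast, and a hypothesis-generating analysis should still address the hypothesis.

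**A confidence interval carries the same information as a paired test.** Largely true. The gain is that the interval is given as description and not judged at the 0.05 threshold.

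**Conclusion.** The concern holds in limited form. The paired tests and the change correlations contain no treatment contrast, yet Objectives and Discussion draw the mechanism reading from observed changes and their correlation with headache. Either analysis can be positive when the two treatments affect the marker equally or not at all. How often depends on quantities that the protocol does not give: from 5% at zero to 18.5% (paired, n = 30) and 34% (pooled correlation, n = 60) at 0.2, and to 56% and 90% at 0.4. The absence of a contrast does not depend on those values.

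The stronger statement, that these tests routinely reject in error when press-needle does nothing, is not supported. It presumes drift and correlation, treats detection of a real association as an error, and cannot be tested here, because the only comparator is active naproxen.

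**What to change.** 1. In Exploratory and safety analyses, drop the within-group paired tests. Report within-arm changes as estimates with confidence intervals, for description only.
2. State that any claim that press-needle changes a marker relative to naproxen rests on the baseline-adjusted ANCOVA, or on the MMRM for heart rate variability.
3. In that section and in Comprehensive mechanism analysis, adjust the marker-headache associations for arm, show them by arm, and call them associations. Adjustment removes the part of a pooled correlation that only reflects arm differences in both variables. It does not turn the association into a treatment effect.
4. In the Discussion, write of association rather than mechanism unless the marker differs between arms. Add that, with an active comparator and no sham arm, the contrast shows only a difference from naproxen and cannot detect a pathway that both treatments share.

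A mediation estimate or a treatment-by-marker interaction is not required; in about 60 women either would be imprecise.

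The cost is wording and a few lines of code on data already planned. The downside is fewer nominally significant exploratory results.

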#### Subgroup and sensitivity analyses

Pre-specified exploratory subgroup analyses will be performed based on menstrual subtype (PMM vs. MRM). Interaction tests between treatment group and menstrual subtype will be performed within the MMRM framework for the primary outcome, with results reported as exploratory (interaction *p*-values reported with 95% CIs). We acknowledge that the trial is not powered for formal subgroup comparisons, and all subgroup findings will be interpreted strictly as hypothesis-generating.

To account for potential expectation effects inherent in the open-label design, baseline “Credibility/Expectation Questionnaire” (CEQ) scores will be collected (19). In the primary analysis, CEQ scores will be included as covariates in the MMRM model to correct for potential expectation-related bias and improve the precision of treatment effect estimates. In addition, exploratory interaction terms (treatment × CEQ score) may be tested to investigate whether baseline expectations moderate treatment response; however, given the pilot nature of this trial, these analyses are strictly hypothesis-generating in nature and will be interpreted descriptively.

Sensitivity analyses will include: (1) PP analysis; (2) ITT analysis without imputation; (3) adjusting for potential baseline imbalances if any are observed.

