### Blinding design

This is an open-label trial. Participants and intervention providers will be aware of the group assignments. To avoid detection bias, outcome assessors and statisticians will remain completely unaware of the group assignments throughout the trial. The following measures will be taken to maintain blinding:(1) Blinded outcome assessors: All outcome assessments will be conducted by trained assessors who were not involved in randomization or treatment administration. Participants will be instructed not to disclose their treatment group to the assessors during any assessment visit;(2) Blinded statisticians: Randomization codes will not be disclosed to the statisticians until the final data lock-in and completion of all pre-specified analyses. The dataset provided to the statistician will include coded treatment indicators (e.g., Group A and Group B) but will not reveal the correspondence to the actual interventions;(3) Data manager blinding: Data managers will use coded group identifiers to process and clean the data. They will not have access to randomization information.

To evaluate the influence of the open-label design, participants’ treatment credibility and expectancy will be assessed at baseline and explored as potential confounders in the analysis of treatment effects.

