#### Assessment of treatment credibility and expectations

At baseline, validated scales (such as the Credibility/Expectancy Questionnaire) will be used to assess participants’ credibility and expectations regarding their assigned treatment. This assessment will be conducted after randomization and before the first treatment session. The questionnaire consists of two subscales: credibility (how reasonable and helpful the treatment appears) and expectations (the extent of improvement the participant anticipates). These scores will be used in exploratory analyses to examine whether baseline expectations moderate treatment response and will be included as covariates in sensitivity analyses to control for potential bias.

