#### Allocation of interventions

Participants who meet all eligibility criteria and provide written informed consent will be formally enrolled and assigned a unique study identification number. A computerized block randomization sequence with a 1:1 allocation ratio (Experimental Group: Control Group) will be generated by an independent statistician not involved in recruitment or intervention delivery, using random block sizes of 4 and 6. The allocation sequence will be concealed using sequentially numbered, opaque, sealed envelopes (SNOSE). Upon enrollment and completion of baseline assessments, the treating acupuncturist will open the next sequentially numbered envelope in the presence of the participant to reveal the group assignment. This process ensures allocation concealment.

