#### Primary outcome analysis

The primary outcome measure—the change in the number of days with moderate-to-severe headaches per menstrual cycle from the last menstrual cycle of the screening period through the end of the 3-month intervention—will be analyzed using a repeated-measure mixed-effects model (MMRM). This model will treat the measurements from each menstrual cycle during the 3-month intervention period as repeated measures, with treatment group, time, and the interaction between treatment and time as fixed effects. The average number of moderate-to-severe headache days from the qualified screening cycles will be included as a covariate, and subject-specific random intercepts will be specified to account for within-subject correlation across the three menstrual cycles.

The primary focus is on the differences in the magnitude of change from baseline across groups at the end of the intervention period (Week 12/Month 3). Results will be presented as adjusted between-group differences, along with their 95% confidence intervals (CI) and corresponding *p*-values. Given that this is a preliminary feasibility study, *p*-values will be interpreted descriptively rather than as confirmatory evidence.

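### Two different primary models are pre-specified, and the one with CEQ scores adjusts for a variable measured after participants know their arm, which can bias the estimated effect of assignment

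*Protocol article*

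**What the plan says.** The role of the CEQ is described in four places in the Protocol article.

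- **Subgroup and sensitivity analyses:** "In the primary analysis, CEQ scores will be included as covariates in the MMRM model to correct for potential expectation-related bias". The same sentence also expects a more precise treatment estimate. A treatment-by-CEQ interaction is optional and exploratory.
- **Primary outcome analysis:** the model is a repeated-measures mixed model "with treatment group, time, and the interaction between treatment and time as fixed effects", plus mean headache days over the qualified screening cycles as a covariate and a random intercept per participant. CEQ is not listed.
- **Assessment of treatment credibility and expectations:** the scores serve exploratory moderator analyses and "will be included as covariates in sensitivity analyses to control for potential bias".
- **Blinding design:** credibility and expectancy are to be "assessed at baseline and explored as potential confounders in the analysis of treatment effects".

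On timing and content, the credibility section says that the CEQ will "assess participants’ credibility and expectations regarding their assigned treatment", and: "This assessment will be conducted after randomization and before the first treatment session". Under Allocation of interventions, the treating acupuncturist will "open the next sequentially numbered envelope in the presence of the participant to reveal the group assignment". Blinding design adds: "Participants and intervention providers will be aware of the group assignments".

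**The concern.** An analyst cannot follow all of these statements. One section defines a primary model without CEQ, another puts CEQ into the primary analysis, and a third makes it a sensitivity covariate. Unless this is settled in advance, the choice could be made after the results are seen.

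The version with CEQ has a further problem. A woman who has just seen her envelope opened and is asked how credible her assigned treatment is gives an answer that the assignment may have changed. Such a score cannot have influenced a randomised allocation, so it is not a confounder. Adjusting for it takes out any part of the effect that runs through expectation. It also opens a non-causal path through any shared cause of CEQ and headache days. The resulting coefficient need not be the effect of assignment, to which the intention-to-treat population commits the trial.

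The Objectives and Sample size sections say that the trial exists to supply an effect size for a later confirmatory trial, so a distorted estimate would carry forward into that trial's sample size.

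**Working it through.** **1. Order of events.** The envelope is opened in front of the participant, participants know their arm, and the CEQ follows randomisation and concerns the assigned treatment. Taken together, these place the CEQ after allocation is known. One tension remains: Allocation of interventions opens the envelope only once baseline assessments are complete, and Table 2 ticks the CEQ at baseline. Table 2 does not settle the order, because its baseline column also contains randomisation. The credibility section is the only one to state the order for the CEQ explicitly, so it is taken to govern.

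**2. The plan's own figure.** 30 evaluable per group with 20% dropout: 30 / 0.8 = 37.5, rounded up to 38 per group, 76 in total. This reproduces the stated sample size, and nothing below changes it.

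**3. Shift caused by adjustment.** Let d be the difference between arms in mean CEQ (in within-arm SDs) and r the size of the within-arm correlation of CEQ with outcome. CEQ is treated as one score. Adjustment moves the treatment coefficient by d × r outcome SDs. The protocol gives neither quantity; both are assumed, with ranges.

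- Low: 0.3 × 0.2 = 0.06 SD
- Central: 0.5 × 0.3 = 0.15 SD
- High: 0.8 × 0.4 = 0.32 SD
- No difference in CEQ between arms: 0 × r = 0, no shift

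**4. Yardstick.** The unadjusted standard error at a single time point is √(2/n): √(2/30) = 0.26 SD, or √(2/38) = 0.23 SD if all 38 per arm contribute. The planned model also uses baseline and three cycles, so its standard error will differ.

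**5. Precision.** The variance changes by (1 − r²) × (1 + d²/4). The first term is the drop in residual variance; the second is the inflation because CEQ is correlated with arm.

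| r | d | Factor |
|---|---|---|
| 0.4 | 0.3 | 0.84 × 1.02 = 0.86 |
| 0.3 | 0.5 | 0.91 × 1.06 = 0.97 |
| 0.2 | 0.8 | 0.96 × 1.16 = 1.11 |

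The result runs from a 14% reduction in variance to an 11% increase.

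**6. Simulation check.** 30 per arm, 2,000 runs per scenario, one time point, assumed total effect −0.50 SD (negative means fewer headache days).

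- Without CEQ in the model, the mean estimate was −0.49 to −0.51 in every scenario.
- With CEQ in the model and no effect of allocation on CEQ, it was about −0.50.
- With a CEQ shift of 0.5 SD and a CEQ effect of −0.3, it was −0.35 (formula: −0.50 + 0.5 × 0.3 = −0.35).
- With the same shift and no CEQ effect, but an unmeasured cause correlated 0.5 with CEQ and with effect −0.5 on outcome, it was −0.38 (formula: −0.50 + 0.5 × 0.5 × 0.5 = −0.375).

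The last case shows distortion even when expectation does nothing to headache.

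**7. Consequence for the next trial.** If 0.50 SD were reported as 0.35 SD, the sample size calculated from it would be multiplied by (0.50/0.35)² = 2.04. A shift in the other direction would leave the next trial too small.

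**The case against.** The strongest reply is that the adjusted model answers a different question. The protocol names expectancy effects as a limitation of the open-label design, and adjustment may be meant to isolate an effect that does not act through expectation. If CEQ only mediates and has no unmeasured common cause with headache days, the coefficient does estimate that effect. This stands as a matter of principle. However, the protocol neither states that target for its primary analysis nor claims the absence of shared causes, and it defines its main population by intention to treat.

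A reader might infer that the primary estimate is certain to be biased, or that a true null would be reported as 0.15 SD. The documents support neither. Bias requires that allocation shifts CEQ and that CEQ affects or shares causes with the outcome, and no CEQ data are given. Under pure mediation, a zero total effect with a non-zero adjusted coefficient reflects two opposing components, which is not an error in itself. Nor can it be said that adjustment never gains precision, since some of the assumed values give a modest gain.

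It also counts that every result is declared exploratory, that the dedicated primary section already omits CEQ, and that the conflicting sentence sits under a heading on subgroup and sensitivity analyses. This lowers the stakes but does not remove the contradiction.

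**Conclusion.** The contradiction over the primary model is on the page and needs no assumption. That the CEQ is a post-allocation variable follows from the stated timing, the wording about assigned treatment and the open-label design.

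The bias is conditional. Comparing two very different treatments open-label makes a CEQ difference plausible, and the protocol itself presumes expectation effects. Neither size nor direction can be derived from the documents; the direction depends on which arm participants find more credible. Over the assumed ranges the shift is modest to substantial: the central 0.15 SD is a little under 0.6 of the 0.26 SD standard error, and the upper 0.32 SD exceeds it. This is worth correcting before data are seen, because the effect estimate is the pilot's main product.

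**What to change.** 1. State that the model in Primary outcome analysis, without CEQ, is the only primary model.
2. Delete the sentence under Subgroup and sensitivity analyses that puts CEQ into the primary analysis, or reword it so that CEQ adjustment and the treatment-by-CEQ term are sensitivity or exploratory only, in line with the credibility section.
3. In Blinding design, stop describing CEQ scores as confounders.
4. Reconcile Allocation of interventions and Table 2 with the credibility section on when the CEQ is given relative to the envelope.

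These are wording changes and leave the sample size at 76. The protocol requires ethics approval for any amendment, so they would go through that route.

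Optionally, if a true baseline covariate is wanted, ask about expectancy for both treatments before the envelope is opened. This is a small added burden on participants, changes how the questionnaire is used, and needs ethics approval, so it is not free.
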